7.1.2. Experimental treatment arm (TS-1-treated arm)

1) Treatment regimen

TS-1 will be administered by the oral route daily for 14 days (Day 1-14) with a 7 day rest period (Day 15-21). The daily dose (80 mg, 100 mg, or 120 mg), which is based on body surface, will be divided into 2 doses daily (after breakfast and dinner) This 21-day (3-week) period will comprise 1 cycle and will be repeated for 1 year from the protocol treatment initiation day (about 18 cycles will be administered). New cycles will not be started after 1 year has elapsed from the protocol treatment initiation date. After completion of UFT treatment, subjects will be followed for up to 5 years (for 3 years after enrollment of the last subject), and antineoplastic therapy will not be performed until metastases or relapse are confirmed.

Daily oral TS-1 treatment for 14 days

7-day rest period

Day 1 Day 14 Day 21

TS-1 dose and administration method

| Body surface area | Single dose at treatment  initiation (FT equivalent) | Daily dose  (FT equivalent) | Breakfast | Lunch | Dinner |
| --- | --- | --- | --- | --- | --- |
| < 1.25 m^2^ | 40 mg/dose | 80 mg | 40 mg | - | 40 mg |
| ≥ 1.25 m^2^ to <1.5 m^2^ | 50 mg/dose | 100 mg | 50 mg | - | 50 mg |
| ≥ 1.5 m^2^ | 60 mg/dose | 120 mg | 60 mg | - | 60 mg |

2) TS-1 specifications

TS-1 Capsules 20: 20 mg FT equivalent per capsule

TS-1 Capsules 25: 25 mg FT equivalent per capsule

7.2. Criteria for changing dose and schedule (Rest days or reduced dose days will be recorded in the chart without fail.)

The following terminology will be used for change criteria.

Rest: A temporary holiday during which drug is not administered during the protocol treatment dosing period after which treatment can be resumed if the conditions are satisfied.

Dose reduction: Administration of less than the specified dose

Discontinuation: The protocol treatment is discontinued, and treatment will not be resumed during the subject’s participation in the study.

7.2.1. Rest criteria and resumption criteria

When starting a TS-1 cycle (after the rest period from the previous cycle) and when performing tests during UFT treatment, it will be confirmed that all test values satisfy the dosing criteria before resuming treatment. When the dosing criteria are not satisfied, treatment will be withdrawn and resumed according to the following criteria.

1) Rest criteria

If the following adverse events which apply to the rest criteria occur during the drug treatment period, drug treatment will be immediately withdrawn, the (sub)investigator will wait until the values return to at least the treatment resumption criteria before resuming treatment.

The (sub)investigator will decide whether or not to withdraw treatment when rest criteria apply to the laboratory values of subjects whose baseline values are close to the rest criteria.

Rest criteria *Non-hematologic toxicities: Adverse events from sections of the CTCAE other than Blood/Bone Marrow

| Parameter | | Criterion for prescribing rest |
| --- | --- | --- |
| Hematologic toxicities | WBC | < 3,000 /mm^3^ |
|  | Neut | < 1,500 /mm^3^ |
|  | PLT | < 75,000 /mm^3^ |
|  | Hb | < 9.0 g/dL |
| Non-hematologic toxicities  * | T.Bil | ≥ 2.0 mg/dL |
|  | AST⋅ALT | ≥ 100 IU/L |
|  | Cr | ≥ 1.2 mg/dL |
|  | Other adverse events | ≥ Grade 2 |
| Other instances in which the investigator determines that rest is necessary because of adverse events, etc., in order to continue the protocol treatment. | | |

2) Treatment resumption criteria

(1) UFT-treated arm

After withdrawing treatment, the investigator will wait until the treatment resumption parameters return to normal to resume treatment. The dose at treatment resumption will be determined in accordance with the dose reduction criteria (refer to 7.2.2.). When the rest period exceeds 28 days due to adverse events, the subject’s protocol treatment will be discontinued.

(2) TS-1-treated arm

After a rest of at least 1 week in the TS-1-treated arm, it will be confirmed that the following treatment resumption criteria have been satisfied before resuming TS-1 treatment. The dose at treatment resumption will be determined in accordance with the dose reduction criteria (refer to 7.2.2.). When the rest period exceeds 28 days due to adverse events, the subject’s protocol treatment will be discontinued.

Example) When rest starts on Day 8 of the first cycle

after at least 1 week of rest, it is confirmed if treatment can be resumed.

→*If treatment can be resumed: the second cycle is started.

*If treatment cannot be resumed: Treatment resumption is postponed until the resumption criteria are satisfied.

However, when the rest period exceeds 28 days, the protocol treatment will be discontinued and only a follow-up will be performed because the discontinuation apply (refer to “7.4 Follow-up at discontinuation of protocol treatment”).

Treatment resumption criteria

*Non-hematologic toxicities: Adverse events from sections of the CTCAE other than Blood/Bone Marrow

| Parameter | | Treatment resumption criterion |
| --- | --- | --- |
| Hematologic toxicities | WBC | ≥ 3,000 /mm^3^ |
|  | Neut | ≥ 1,500 /mm^3^ |
|  | PLT | ≥ 100,000 /mm^3^ |
|  | Hb≥ | ≥ 9.0 g/dL |
| Non-hematologic toxicities* | T.Bil | < 1.5 mg/dL |
|  | AST⋅ALT | < 100 IU/L |
|  | Cr | < 1.2 mg/dL |
|  | Other adverse events | ≤ Grade 1 |

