7.3. Discontinuation of protocol treatment

The protocol treatment will be discontinued if any of the following conditions apply.

1) Confirmed metastasis or relapse of primary disease

2) Confirmed secondary cancer (double cancer)

3) Subject has died.

4) The TS-1 dose is < 80 mg/day or the UFT dose is < 300 mg/day, as a result of applying the dose reduction criteria

5) The rest period exceeds 28 days.

6) The subject withdraws consent for the protocol treatment (TS-1 or UFT treatment).

7) The subject’s ability to keep appointments is compromised by transferring hospitals, etc.

8) The subject is found to be ineligible after enrollment.

9) The (sub)investigator otherwise determines that continuation of the protocol treatment is compromised.

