# Statistical Considerations

12.1. Rationale for target sample size

The results of large-scale comparative studies in Western countries were used as the rationale for the disease-free survival rate in the control arm. This was done because there are no reports of Japanese studies in which UFT treatment was performed on control subjects as in the present study that could be evaluated.

The 3-year disease-free survival rate among subjects that had undergone curative therapy for Stage III, IVA, and IVB squamous cell cancers of the head and neck was approximately 35-45% in subjects that received radiotherapy postoperatively and approximately 40-59% in subjects that received combination radiotherapy and chemotherapy postoperatively.

From these results, it was hypothesized that the 3-year disease-free survival rate would be 50% in the control (UFT) arm. Thus, 216 subjects per arm would be required to have a hazard ratio of 0.7 (3-year disease-free survival rate: 61.6%) for the test (TS-1) arm versus the control arm with an enrollment period of 3 years, follow-up period of 3 years, two-sided α of 0.05, and statistical power of 80%. A sample size of 250 subjects per arm (500 in both arms) was selected because a power of test of at least 80% could be guaranteed with 250 subjects per arm.

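### Section 7.2.1 states the rule for resuming treatment after a rest inconsistently and, read literally, sets a different condition for each arm

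*Protocol*

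**What the plan says.** Four statements in section 7.2.1 bear on when treatment may restart.

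- **Opening paragraph, both drugs named.** For a new TS-1 cycle and at tests during UFT treatment, "it will be confirmed that all test values satisfy the dosing criteria before resuming treatment".
- **Item 1), rest criteria, no arm distinguished.** After a rest for an adverse event, "the (sub)investigator will wait until the values return to at least the treatment resumption criteria before resuming treatment".
- **Item 2)(1), UFT.** After treatment is withdrawn, "the investigator will wait until the treatment resumption parameters return to normal to resume treatment".
- **Item 2)(2), TS-1.** After at least 1 week of rest, "it will be confirmed that the following treatment resumption criteria have been satisfied before resuming TS-1 treatment".

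One table of resumption criteria follows the TS-1 text and its worked example. It has no arm label. It lists WBC at least 3,000, neutrophils at least 1,500 and platelets at least 100,000 /mm³; Hb at least 9.0 g/dL; total bilirubin below 1.5 mg/dL; AST and ALT below 100 IU/L; creatinine below 1.2 mg/dL; and other adverse events of Grade 1 or less.

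The time limit is the same in both arms: "When the rest period exceeds 28 days due to adverse events, the subject’s protocol treatment will be discontinued". Section 7.3 repeats it as a reason for stopping: "The rest period exceeds 28 days". Section 7.2 defines discontinuation as permanent for the subject's time in the study.

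**The concern.** A site restarting treatment in the UFT arm has two instructions. The common rule sends it to the resumption criteria. The arm-specific sentence sends it to an undefined normal. A site restarting TS-1 is sent to the criteria both times. The trial is open-label, so each site knows which sentence applies to its patient.

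The 28-day limit gives the wording practical weight. A subject who cannot meet the resumption condition in that time leaves protocol treatment for good, and section 7.6 then bars antineoplastic drugs until relapse, secondary cancer or 3 years after the last enrolment. If sites follow the two sentences as written, subjects with the same clinical course could continue in one arm and stop in the other. Time on treatment would then depend partly on wording and not only on how each drug is tolerated.

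**Working it through.** The plan gives no figure on this point, so there is nothing to recompute. The check compares the text.

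**Step 1: does the conflict depend on which arm the table belongs to?**

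- If the table governs both arms, the UFT sentence differs from it: the table sets thresholds and allows Grade 1, while the sentence asks for normal.
- If the table governs TS-1 only, UFT has no stated thresholds, and the common rule in item 1) refers UFT subjects to criteria that do not exist for them.

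The text is inconsistent on either reading.

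**Step 2: is the UFT wording stricter in the document's own terms?**

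- *Other adverse events.* Rest is triggered at Grade 2 or above, and the table allows restart at Grade 1 or less. A Grade 1 event is still an adverse event, so it is not normal in the plain sense. The UFT sentence is stricter on this row, and no outside reference range is needed to see it.
- *Laboratory rows.* The protocol gives no normal ranges. Whether normal is stricter than, say, Hb at least 9.0 g/dL or WBC at least 3,000 /mm³, and by how much, cannot be shown from the document.

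**Step 3: follow one course through both arms.** A subject rests for a Grade 2 non-haematological event. It improves to Grade 1 after the first week and stays there beyond day 28 of the rest. All laboratory values meet the table.

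| Rule applied | Outcome |
| --- | --- |
| TS-1 sentence and table | may resume: minimum 1-week rest served, Grade 1 accepted |
| UFT sentence, read literally | may not resume; discontinued when the rest exceeds 28 days |
| Common rule in item 1), with the table applied to UFT | may resume |

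The two UFT rows differ, although both come from section 7.2.1.

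**Step 4: could this course occur?** Subjects enrol within 3 months of completing curative therapy (section 5.1). Section 9.1.1 records baseline grades of fatigue, weight loss, mucositis, anorexia and other symptoms, so low-grade symptoms at entry are foreseen. How often such a course occurs is not stated.

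**Step 5: does another provision remove the conflict?** Section 7.2.1 lets the (sub)investigator decide whether to withdraw treatment when baseline laboratory values are close to the rest criteria. That covers starting a rest on laboratory grounds. It does not cover resumption or a persisting symptom.

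**The case against.** The strongest reply is that this is loose wording and not a second rule. The heading of item 2) covers both arms, the table repeats that heading without an arm label, and the parameters named in the UFT sentence are listed nowhere else. Section 7.2.3 uses similar wording about recovery of adverse events in general. One table for both arms, with normal meaning that the table is met, is a coherent reading and may be what was intended. This stands as an account of intent. It does not settle what a site should do, because the UFT sentence neither cites the table nor repeats its thresholds.

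Three further points stand:

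- The common rule says "wait until the values return to at least the treatment resumption criteria before resuming treatment". The words *at least* make it a floor, so a stricter UFT condition is inconsistent with it but does not strictly contradict it.
- The asymmetry is not all one way. TS-1 alone has a minimum 1-week rest, and in the worked example a rest from Day 8 is followed by the second cycle.
- Subjects who stop are still followed (section 7.4) and, if eligible, stay in the analysis set (section 12.2).

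A reader might infer that the wording tilts the efficacy comparison towards TS-1 by cutting exposure in the control arm. The documents do not support that. It requires UFT exposure to drive disease-free survival, whereas section 2.4.2 says adjuvant benefit is not established for overall or disease-free survival. Section 2.2 reports non-significant 3-year differences for UFT against no treatment (survival 77.9% versus 72.9%, relapse-free 73.4% versus 66.2%), although distant relapse was significantly lower (7.9% versus 14.6%). The TS-1 minimum rest also limits exposure in the other arm. A reader might also want a count of affected subjects. With no rest rates in the protocol, any count would only restate an assumed percentage of the 250 in the UFT arm.

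**Conclusion.** The point holds as an inconsistency in an operating rule. Section 7.2.1 gives a common resumption rule, a UFT sentence that departs from it in undefined terms, and a TS-1 sentence that refers to the listed criteria. Followed literally, the UFT condition is stricter on the row for other adverse events, and the shared 28-day limit can turn that difference into permanent discontinuation.

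This rests on the plain meaning of normal and on sites following the arm-specific sentence. If sites read that sentence as meeting the table, the stricter UFT condition disappears. The size and direction of any effect on disease-free survival cannot be determined from the document. It should still be corrected, because sites act on the text as written and the correction is cheap.

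**What to change.** Reconcile the statements in section 7.2.1 (opening paragraph, item 1), items 2)(1) and 2)(2), and the resumption table). State explicitly whether the table governs both arms. If the arms are meant to differ, give the reason and say what normal means for UFT. Which criteria apply in either arm is for the clinical team.

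The cost is a one-sentence protocol clarification and a note to sites. Sample size and analysis methods do not change. Section 9.1.2 already lists rest dates and reasons and discontinuation reasons among the observations, so the team could also check by arm how many rests passed 28 days.

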7.2.2. Dose reduction criteria

When the following adverse event criteria apply during a rest period, treatment will be resumed according to the dose reduction criteria.

| Adverse event criteria for reducing dose | | |
| --- | --- | --- |
| Hematologic toxicities | WBC | < 2,000 /mm^3^ (≥ Grade 3) |
|  | Neut | < 1,000 /mm^3^ (≥ Grade 3) |
|  | PLT | < 50,000 /mm^3^ (≥ Grade 3) |
|  | Hb | < 8.0 g/dL (≥ Grade 3) |
| Non-hematologic toxicities* | T.Bil | ≥ 3 mg/dL |
|  | AST⋅ALT | ≥ 150 IU/L |
|  | Cr | ≥ 1.2 mg/dL |
|  | Other adverse events | ≥ Grade 3 |
| Other instances in which the investigator determines that dose reduction is necessary because of adverse events, etc., in order to continue the protocol treatment. | | |

* Non-hematologic toxicities: Adverse events from sections of the CTCAE other than Blood/Bone Marrow

Dose reduction will be performed according to the following dose reduction criteria.

1) TS-1 dose reduction criteria

Dose reduction will be performed 1 level at a time, and the minimum dose will be 80 mg/day.

| Body surface area | Starting dose  (FT equivalent) | TS-1 dose level | | |
| --- | --- | --- | --- | --- |
|  |  | 1st dose reduction | 2nd dose reduction | 3rd dose reduction |
| < 1.25 m^2^ | 80 mg/day | Discontinuation | - | - |
| ≥ 1.25 m^2^ to < 1.5 m^2^ | 100 mg/day | 80 mg/day | Discontinuation | - |
| ≥ 1.5 m^2^ | 120 mg/day | 100 mg/day | 80 mg/day | Discontinuation |

2) UFT dose reduction criteria

The minimum dose will be 300 mg/day.

| Body surface area | Starting dose  (FT equivalent) | UFT dose level | |
| --- | --- | --- | --- |
|  |  | 1st dose reduction | 2nd dose reduction |
| < 1.5 m^2^ | 300 mg/day | Discontinuation | - |
| ≥ 1.5 m^2^ | 400 mg/day | 300 mg/day | Discontinuation |

7.2.3. Criteria for dose elevation after administration of reduced dose

Dose will not be increased for subjects receiving a reduced dose, even if the relevant adverse events return to normal.

7.3. Discontinuation of protocol treatment

The protocol treatment will be discontinued if any of the following conditions apply.

1) Confirmed metastasis or relapse of primary disease

2) Confirmed secondary cancer (double cancer)

3) Subject has died.

4) The TS-1 dose is < 80 mg/day or the UFT dose is < 300 mg/day, as a result of applying the dose reduction criteria

5) The rest period exceeds 28 days.

6) The subject withdraws consent for the protocol treatment (TS-1 or UFT treatment).

7) The subject’s ability to keep appointments is compromised by transferring hospitals, etc.

8) The subject is found to be ineligible after enrollment.

9) The (sub)investigator otherwise determines that continuation of the protocol treatment is compromised.

7.4. Follow-up at discontinuation of protocol treatment

Except for the subjects listed below, every effort will be made to follow-up for survival, metastasis, and relapse all of the subjects who discontinued the protocol treatment, based on the provisions in 7.3. If metastasis or relapse is confirmed, only outcome will be followed up.

1) The subject died.

2) The subject withdrew consent to be followed up.

3) The subject was found to be ineligible after beginning the protocol treatment.

4) Follow-up was compromised for some other reason.

Follow-up after treatment discontinuation will be performed every 3-6 months, counting from the starting day of the protocol treatment.

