7.1.1. Control treatment arm (UFT treated arm)

1) Treatment regimen

UFT will be administered daily by the oral route for 1 year. The daily dose (300 mg or 400 mg), based on body surface, will be divided into 2 doses daily (after breakfast and dinner) or 3 doses daily (after breakfast, lunch, and dinner). After completion of UFT treatment, subjects will be followed for up to 5 years (for 3 years after enrollment of the last subject), and antineoplastic therapy will not be performed until metastases or relapse are confirmed.

Daily oral UFT treatment for 1 year

Day 1 1 year

UFT dose and administration method

| Body surface area | Single dose at treatment initiation (FT equivalent) | Daily dose  (FT equivalent) | Breakfast | Lunch | Dinner |
| --- | --- | --- | --- | --- | --- |
| < 1.5 m^2^ | 100 mg | 300 mg | 100 mg | 100 mg | 100 mg |
|  | 150 mg (granules) |  | 150 mg | - | 150 mg |
| ≥ 1.5 m^2^ | 200 mg | 400 mg | 200 mg | - | 200 mg |

2) UFT specifications

UFT capsules: 100 mg FT equivalent per capsule

UFT E granules: 200 mg FT equivalent per gram

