7.6. Therapy following protocol treatment

This protocol does not specify any therapy after discontinuing the protocol treatment at relapse or developing secondary cancer. However, after discontinuation of the protocol treatment for other reasons and after completion of the protocol treatment, antineoplastics will not be administered until relapse or secondary cancer occurs or until 3 years have elapsed from enrollment of the last subject.

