9.1.3. At follow-up

1) Testing dates

The observations and tests listed below will be performed every 3-6 months, counting from the first day of the protocol treatment. Follow-up will be performed for 3 years after the enrollment of the last subject. Entries in case report forms will be made once annually until Year 3, after which all tests and observations will be performed 3 years after the enrollment of the last subject.

2) Observations and tests

Outcome

Confirmation of outcome: Survival (date of last confirmation of survival)

Death (Cause of death: primary disease, other cancer, other, date of death)

Lost to follow-up (date of last confirmation of survival)

Method of confirmation: clinic appointment, other

*When survival status cannot be confirmed directly because the subject transferred to another hospital or the like, every effort will be made to obtain outcome information from the subject’s new hospital.

Confirmation of relapse and secondary cancer

Presence of relapse (If present, the following items will be entered in the outcome report.)

Relapse site: local, distant (brain, bone, lung, liver, lymph node, adrenal gland, skin, other)

Confirmation method and date confirmation performed: simple chest radiography, ultrasonography, CT, MRI, PET, histopathology, cytology, other

Confirmation date (If diagnosed by multiple diagnostic methods, the date the earliest test was performed.)

Presence of secondary cancer (If present, the following items will be entered in the outcome report.)

Site of occurrence of secondary cancer (head and neck, lung, esophagus, stomach, other)

Diagnostic method and date diagnosis performed: simple chest radiography, ultrasonography, CT, MRI, PET, histopathology, cytology, other

Date of diagnosis (If diagnosed by multiple diagnostic methods, the date the earliest test was performed.)

*Presence of relapse and secondary cancer will be confirmed in accordance with “Definition of relapse and secondary cancer” in 11.1.

Therapy following protocol treatment: Presence of therapy following protocol treatment

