11.1. Primary endpoint

Disease-free survival (DFS)

The period from the enrollment date to earliest date among the date that relapse was diagnosed, date that secondary cancer was diagnosed, and date of death from any cause. For survivors not diagnosed with relapse or secondary cancer, DFS will be cut off at the last survival confirmation date.

Definition of relapse and secondary cancer

∙Definition of relapse and relapse confirmation date

“Relapse” will be diagnosed when any of the following criteria apply.

(1) Findings on diagnostic imaging (simple chest radiography, ultrasonography, CT, MRI, PET, etc.) that are not secondary cancer will be considered “relapse.” When relapse is diagnosed by multiple diagnostic methods, the date of the earliest test will be considered the “relapse confirmation date.”

(2) When relapse is diagnosed by pathological tests (cytology, biopsy), the date of the earliest test will be considered the “relapse confirmation date.”

(3) An increase in tumor markers will not be considered “relapse.”

∙Definition of secondary cancer (double cancer, multiple cancer) and secondary cancer confirmation date

(1) Definition of secondary cancer

Findings satisfying all of the criteria below from Warren and Gates Diagnostic Criteria 1) will be considered “secondary cancer.”

(1) Each of the tumors exhibits clear malignancy.

(2) Each of the tumors is separate and distinct.

(3) One tumor is not a metastasis of the other.

(2) Definition of secondary cancer confirmation date

(1) When there are findings on diagnostic imaging (simple chest radiography, ultrasonography, CT, MRI, PET, etc.), the date of the imaging will be considered the “confirmation date” and when secondary cancer is diagnosed by multiple diagnostic methods, the date of the earliest test will be considered the “secondary cancer confirmation date.”

(2) When secondary cancer is diagnosed by pathological tests (cytology, biopsy), the date of the earliest test will be considered the “confirmation date.”

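### Section 7.4 does not name secondary cancer in follow-up after treatment discontinuation, at odds with the DFS definition and section 9; separately, the bar on later antineoplastic therapy ends at different events in different sections

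*Protocol*

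**What the plan says.** **Endpoint.** Section 11.1 runs DFS from enrollment to the "earliest date among the date that relapse was diagnosed, date that secondary cancer was diagnosed, and date of death from any cause". On censoring it says: "For survivors not diagnosed with relapse or secondary cancer, DFS will be cut off at the last survival confirmation date".

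**Follow-up after stopping treatment.** Section 7.4 says that "every effort will be made to follow-up for survival, metastasis, and relapse all of the subjects who discontinued the protocol treatment", every 3 to 6 months from the start of protocol treatment. Once metastasis or relapse is confirmed, only outcome is followed.

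**General follow-up.** Section 9.1.3 says: "The observations and tests listed below will be performed every 3-6 months, counting from the first day of the protocol treatment". Its list includes "Presence of secondary cancer (If present, the following items will be entered in the outcome report". The reporting table in section 9.2 and the Schema run outcome reporting from discontinuation or completion of treatment to 3 years after the last enrollment.

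**Later antineoplastic therapy.** Section 7.1.1 says that after treatment is completed "antineoplastic therapy will not be performed until metastases or relapse are confirmed", and section 7.1.2 repeats the sentence. Section 7.6 says that, after completion or after discontinuation for other reasons, "antineoplastics will not be administered until relapse or secondary cancer occurs", or until the 3-year follow-up point. Section 7.5.1 also lifts its prohibition at relapse or secondary cancer.

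**The concern.** The rule written for subjects who stop the drug is narrower than the primary endpoint it serves. A site is likely to open 7.4 when a subject stops treatment, and 7.4 does not refer to 9.1.3.

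The censoring rule adds to the risk. DFS is cut off at the last date of confirmed survival, not the last disease assessment. A second cancer that nobody looked for would therefore count as disease-free time until a later relapse, death or last contact.

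The second conflict concerns subjects who completed treatment. Two sets of sections give different answers on whether the bar on antineoplastic therapy still applies once a second cancer is confirmed. That bears directly on the care of those subjects, and sites could act differently.

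**Working it through.** The point rests on wording, so the check sets the sections side by side.

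**1. Can secondary cancer be read into the 7.4 list?** No. Section 7.3 lists metastasis or relapse of the primary disease and secondary cancer as separate reasons for discontinuation. Section 11.1 defines relapse on imaging as findings that are not secondary cancer. The omission in 7.4 is therefore a real difference in scope.

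**2. Do other sections cover the same subjects?** Yes.

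| Section | Applies after discontinuation? | Secondary cancer named? |
| --- | --- | --- |
| 7.4 | Yes, written for it | No |
| 7.6 | Yes, expressly | Yes, as an event that ends the restriction |
| 9.1.2 | Imaging or pathology every 3–6 months from treatment initiation | Yes |
| 9.1.3 | Yes, same interval and clock as 7.4 | Yes, with site, method and date |
| 9.2, imaging footnote | Row spans the whole schedule | Yes |
| 9.2, outcome report, and Schema | From discontinuation or completion | Via 9.1.3 |

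One row in 9.2 is softer: confirmation of relapse and secondary cancer is left to clinical symptoms. The imaging footnote in the same table still prescribes tests every 3–6 months.

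**3. Does the sentence in 7.4 limiting follow-up to outcome lose DFS events?** No. It applies once metastasis or relapse is confirmed, and such a subject already has a DFS event.

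**4. The therapy restriction.**

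| Sections | Subjects | Bar lifted at |
| --- | --- | --- |
| 7.1.1, 7.1.2 | Completed treatment | Metastasis or relapse |
| 7.5.1 | On protocol treatment or in follow-up | Relapse or secondary cancer |
| 7.6 | Completed, or discontinued for other reasons | Relapse or secondary cancer (or the 3-year point) |

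The sentence in 7.1.2 refers to UFT although it stands in the TS-1 section. I read it as meant for TS-1. For a subject who completed treatment and has a second cancer without relapse, the first row still bars therapy and the other two no longer do. Subjects who discontinue because of a second cancer are outside this conflict: 7.6 leaves their later therapy unspecified.

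**5. Do the plan's figures change?** No. Section 12.1 gives 50% control 3-year DFS, a hazard ratio of 0.7, 3 years of enrollment, 3 years of follow-up, two-sided α of 0.05 and 80% power. The test-arm rate is 0.50^0.7 = 0.616, as stated. With exponential survival and uniform accrual, the event probability is p = 1 − (e^(−3λ) − e^(−6λ))/(3λ):

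- UFT: λ = ln 2/3, p = 0.639.
- TS-1: λ = 0.7 × ln 2/3, p = 0.512.

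The Schoenfeld formula needs 247 events and Freedman's needs 253. Dividing by 0.639 + 0.512 gives 215 and 220 per arm, against the stated 216. With 250 per arm, 250 × (0.6393 + 0.5123) ≈ 288 events and power is 85.7%.

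For scale only, power = Φ(√D × |ln 0.7|/2 − 1.96), where D is the number of recorded events and the hazard ratio is held at 0.7. The share unrecorded is an assumption; the documents give none.

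| Assumed share of all DFS events unrecorded | Power |
| --- | --- |
| 0% | 85.7% |
| 5% | 83.9% |
| 10% | 81.9% |
| 15% | 79.7% |
| 20% | 77.2% |

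**The case against.** The strongest reply is that the protocol already collects second cancers in these subjects. Sections 9.1.2, 9.1.3 and 9.2 prescribe the checks and the report, and 7.6 presupposes them. The list in 7.4 does not say that nothing else is followed, and a short list that leaves out an item is not a rule against collecting it. This stands. It defeats the inference, which a reader might draw from 7.4 alone, that second cancers are excluded for subjects who stop treatment. It does not remove the inconsistency.

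A reader might also infer that the omission favors TS-1, because section 2.4.1 says the drug causes many adverse reactions and more TS-1 subjects might stop. The documents do not support this. Section 2.4.1 also says the 2-week/1-week schedule was chosen to limit discontinuation and was found feasible, with few adverse reactions. The reduction tables in 7.2.2 point away from earlier stopping on TS-1:

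| Body surface area | Reductions before discontinuation, TS-1 | UFT |
| --- | --- | --- |
| ≥ 1.5 m² | 2 | 1 |
| 1.25 to < 1.5 m² | 1 | 0 |
| < 1.25 m² | 0 | 0 |

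At no body size does this rule stop TS-1 after fewer reductions than UFT. A calculated bias would also have to assume that every second cancer in these subjects is missed, against section 9.

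Finally, the therapy conflict is a separate matter. It concerns subjects who completed treatment and is no evidence of missed endpoint events in those who discontinued. That is correct, and the two points are kept apart here.

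**Conclusion.** Two conflicts between operative rules stand.

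First, 7.4 is narrower than the DFS definition and than 9.1.3 and 9.2 for the same subjects. The consequence is a risk of under-ascertainment at sites that rely on 7.4 alone. No direction of bias, hazard-ratio shift or type I error figure can be derived, because neither the second-cancer share nor discontinuation by arm is given. On the assumed range above, planned power would stay above 80% with 10% of all DFS events unrecorded and fall just below it at 15%. Section 9 gives no ground for expecting losses of that order. For the endpoint this is a minor wording fault.

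Second, for a subject who completed treatment and then has a confirmed second cancer without relapse, 7.1.1 and 7.1.2 contradict 7.5.1 and 7.6 on antineoplastic therapy. This needs no assumption beyond reading the 7.1.2 sentence as meant for TS-1. It affects patient care and must be resolved. Which rule is right is not for this review to say.

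**What to change.** - In 7.4, add secondary cancer to the list of what is followed after discontinuation, and state that the relapse and secondary-cancer checks of 9.1.3 and 9.2 apply unchanged to subjects who discontinued.
- Reconcile 7.1.1 and 7.1.2 with 7.5.1 and 7.6, so that a single rule on antineoplastic therapy covers subjects with a confirmed second cancer. Correct the drug named in the 7.1.2 sentence at the same time.

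The cost is a phrase and a cross-reference in 7.4 and aligned wording in the therapy sections. No visit, test or report form is added, because 9.1.3 and the outcome report already carry the secondary-cancer item. The sample size is unaffected.
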